#### Criteria for discontinuing or modifying allocated interventions {11b}

Participants are free to withdraw from the study at any time. Participants will be withdrawn from the study if they develop any contraindications:Become pregnantReceive a metal implantDevelop seizuresBegin taking tricyclic anti-depressants, neuroleptics/ anti-psychotic or anti-seizure medications;Are no longer fit to participate (e.g. MS relapse or change in disease modifying therapy or prescribed high dose steroids) at clinical PI discretion; test positive for COVID-19; or as an urgent safety measure.

The sponsor, Health and Medical Human Research Ethics Committee (HMHREC) or Therapeutic Goods Administration (TGA) may determine it is within the best interest of study participants or the trial to terminate the study and discontinue the intervention for enrolled participants. Written confirmation will be given to the CI. This may be due to but not limited to serious safety concerns, success or failure of the primary outcome, serious breaches, acts of fraud, critical findings or persistent non-compliance that negatively impacts the patient safety or data integrity. If the study is terminated early, appropriate follow-up and care of participants will be arranged.

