### Plans to promote participant retention and complete follow-up {18b}

If a participant misses more than 3 consecutive intervention visits, they will be considered protocol non-compliant. These participants will be permitted to continue in the study until the end of the 5-week intervention phase, and remain in the study to complete follow-up safety and PROMs, but will be excluded from the follow-up MRI. Outcome measures are collected at the final intervention visit (face to face) and then again 4 months after group allocation. An automatic email is sent to remind participants to complete PROMs via REDCap. Additionally, participants will be contacted three times by two different methods before they are considered ‘lost to follow up’.

Protocol deviations will be monitored monthly by the trial management group and appropriate corrective and preventative actions taken to reduce incidence of protocol deviations. The statistical analysis plan will include per protocol analysis and intention to treat analysis for AE and participant-reported outcomes. As the follow-up MRI will only be conducted for participants without substantial protocol deviations, intention to treat analysis is not possible.

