##### Participant-reported questionnaire and Floodlight data

Continuous outcomes (AQol8D, HADS, FSS, U-Turn speed and Draw a Shape tracing error) will be compared between rTMS and sham conditions with univariate mixed-ANOVAs, as described above for MRI. Significant time by intervention interactions will be followed up with simple effects tests, comparing rTMS to sham group means within each time point.

Outcomes with count data (e-SDMT, Pinching, tracing error in the Draw a Shape test) will be analysed using Mann-Whitney *U* test to compare medians between rTMS and sham groups within each time point. The time by intervention interaction will also be examined using Mann-Whitney *U* tests on within-subject change from baseline, separately for the post-intervention and follow-up timepoints, controlling for false positives using FDR set at 5% threshold.

The statistical analyses carried out may be modified based on distributions observed and test assumptions. For all statistics, the level for significance will be set at *p*<0.05. Summary statistics will be prepared with means and standard deviations considered for normally distributed outcomes or median and interquartile range for non-normally distributed outcomes, as appropriate.

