### Operational issues and modifications in response to COVID-19

COVID-19 and any future global pandemics are a new risk that need to be considered for both researchers and participants. All participants will be counselled about COVID-19 symptoms and risks and asked not to attend study visits if they have any COVID-19 symptoms. They will be screened for COVID-19 symptoms at the entrance to the Menzies each day. Researchers and participants will wear personal protective gear to reduce risk. Physical distancing will be maintained as much as possible, with the exception of the 6 min required to deliver the study intervention. Participants reporting or displaying COVID-19 symptoms will be asked to have the COVID-19 test. If they test positive, they may be withdrawn from the study intervention and MRI follow-ups; we will complete study questionnaires and assessments remotely (via phone or online). They may be replaced in the study by a new participant recruited. If the participant tests negative, they will remain in the study and be allowed to return to continue with study visits. As the COVID-19 situation develops, we will take urgent safety measures as required to ensure the safety of participants and researchers are upheld at all times, following government and local guidelines.

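### The discontinuation rule withdraws participants from the study rather than from stimulation, which conflicts in scope with the COVID-19 section and, read literally, ends the symptom follow-up that the promised intention-to-treat analysis needs

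*Protocol article*

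**What the plan says.** Three sections of the protocol article deal with participants who stop stimulation early.

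- **Criteria for discontinuing or modifying allocated interventions {11b}.** The rule is: "Participants will be withdrawn from the study if they develop any contraindications". The list covers pregnancy, a metal implant, seizures, and starting a tricyclic, antipsychotic or antiseizure drug. A final item covers loss of fitness to take part (relapse, change of disease-modifying therapy or high-dose steroids are the examples), refers to clinical PI discretion, and runs on to "test positive for COVID-19; or as an urgent safety measure". Nothing is said about data collection after withdrawal.
- **Operational issues and modifications in response to COVID-19.** After a positive test, "they may be withdrawn from the study intervention and MRI follow-ups; we will complete study questionnaires and assessments remotely". The section adds: "They may be replaced in the study by a new participant recruited".
- **Plans to promote participant retention and complete follow-up {18b}.** On missed sessions the rule reads: "If a participant misses more than 3 consecutive intervention visits, they will be considered protocol non-compliant". These people nevertheless "remain in the study to complete follow-up safety and PROMs", without the second MRI. The section commits the analysis plan to "per protocol analysis and intention to treat analysis for AE and participant-reported outcomes".

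Symptoms are measured at baseline, after the last session and 4 months after allocation (Secondary outcomes). Continuous symptom scores "will be compared between rTMS and sham conditions with univariate mixed-ANOVAs". Count outcomes are compared by Mann-Whitney tests at each time point and on change from baseline. The missing-data section {20c} prescribes listwise deletion for these outcomes.

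**The concern.** Stopping stimulation and leaving the study are different events. An intention-to-treat analysis needs outcome data from people who have stopped treatment, and {11b} as worded sends them out of the study. None of its triggers makes a questionnaire or a phone test unsafe, and the protocol already allows remote collection at the 4-month follow-up.

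The result is uneven: someone who misses more than three consecutive sessions is followed, while someone who starts an antiseizure drug is, on a literal reading, not. Some triggers are plausibly related to what is measured. A new psychotropic or antiseizure drug, a relapse or a steroid course can go with changes in anxiety, depression, fatigue or quality of life. If such losses differed between the arms in number or in outcome, the symptom comparison would be distorted, and for those people it would be a complete-case analysis and not intention to treat.

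**Working it through.** The point rests on comparing the texts. There is no figure in the plan to reproduce.

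**1. Scope and force of the rules, trigger by trigger**

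| Trigger | Rule in {11b} | Follow-up expressly kept elsewhere? |
|---|---|---|
| Pregnancy, implant, seizures, listed drugs | Mandatory; leaves the study | No |
| Relapse, therapy change, high-dose steroids | Clinical PI discretion; leaves the study | No |
| Positive COVID-19 test | Leaves the study; mandatory or discretionary is unclear from the punctuation | Yes, in the COVID-19 section |
| More than 3 consecutive missed visits | Not listed | Yes, in {18b} |

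For COVID-19 the two rules differ in scope: the whole study against stimulation and MRI. Whether they also differ in force cannot be settled, because the discretion clause in {11b} may reach the COVID-19 item, and the COVID-19 section is itself permissive.

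**2. Data left after a literal withdrawal**

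- Planned symptom time points: baseline, post-intervention, 4 months = 3.
- Withdrawal before visit 20: 3 − 2 = 1 remains (baseline). With no repeated value the person cannot enter the time-by-group mixed ANOVA, and with no change score cannot enter the Mann-Whitney tests on change. Only the baseline cross-section can use them.
- Withdrawal after visit 20 but before 4 months: 2 remain. Listwise deletion still removes the person from the mixed ANOVA, but the Mann-Whitney tests can use the visit-20 value.
- Under the COVID-19 section's rule, none of the 3 need be lost.

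**3. Scale of one loss (any cause)**

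Inputs: 20 recruited (Trial status); 2:1 allocation, blocks of 6, stratified by sex (Sequence generation {16a}). The actual arm sizes are not given. Enumerating every split of 20 across two strata, with 4:2 blocks and part-filled last blocks, gives 4 to 8 sham and 12 to 16 rTMS. I assume 13 and 7, with equal variances; the standard error of the arm difference is proportional to √(1/n₁ + 1/n₂).

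- Share of arm, one sham loss: 1/7 = 14% (1/8 = 12.5% to 1/4 = 25%).
- Share of arm, one rTMS loss: 1/13 = 8% (1/16 = 6% to 1/12 = 8%).
- Standard error, one sham loss: √(1/6 + 1/13) / √(1/7 + 1/13) = 1.053, so about 5% larger (8 sham and 12 rTMS: 1.042; 4 and 16: 1.125).
- Standard error, one rTMS loss: √(1/7 + 1/12) / √(1/7 + 1/13) = 1.014, so about 1% larger (4 and 16: 1.007; 8 and 12: 1.018).

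These figures describe losing any one participant for any reason. They show how small the arms are; they do not measure the effect of this rule.

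**The case against.** The best defence is that {11b} sits under a heading about allocated interventions, so its authors probably meant withdrawal from stimulation. For COVID-19 the later section is the fuller and more specific rule; staff would use it and lose no questionnaires. Section {18b} offers a further route: a person stopped with more than three sessions left will also miss more than three consecutive visits, and such people stay in follow-up. A condensed article need not restate follow-up for every trigger, and recruitment had closed with the last visit expected by the end of December 2021.

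Much of this stands. The intent was probably to keep symptom follow-up, {18b} overlaps with {11b} without contradicting it, and few participants may be affected. But the operative sentence names the study, while the COVID-19 section names the study intervention when it means that. For the mandatory triggers other than COVID-19, no text puts {18b} above {11b}. This is a rule stated with the wrong scope, not a detail left to a longer document.

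A reader might infer more than the documents support:

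- *That every relapse or steroid course ends data collection.* Those withdrawals are discretionary, so nothing is lost automatically.
- *That the two COVID-19 rules also conflict as mandatory against optional.* The punctuation does not settle this.
- *That the symptom results are biased.* Bias needs losses that differ between the arms, and the documents give neither a number of withdrawals nor a difference.
- *That the primary safety result is compromised.* It counts participants with at least one adverse event, and the triggering event will often itself count as one.

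**Conclusion.** The concern holds as a conflict of scope. Section {11b} removes participants from the study where the COVID-19 section removes them only from stimulation and MRI. For pregnancy, implant, seizures and the listed drugs, withdrawal is mandatory with no text that keeps follow-up; for relapse, therapy change and steroids it is discretionary but of the same scope. Followed literally, each withdrawal before visit 20 costs 2 of 3 symptom time points and takes that person out of the comparisons of change, contrary to the intention-to-treat commitment in {18b}.

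The consequence is limited to exploratory symptom outcomes. The number of such withdrawals and the direction and size of any bias are unknown. The conclusion assumes that staff apply the sentence as written; if they already treat it as stopping stimulation only, the data are safe and only the text is wrong. It is worth correcting because the correction is nearly free and lowers the risk of attrition bias in data meant to inform a later efficacy trial.

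**What to change.** 1. In {11b}, make the study intervention, and MRI where it is contraindicated, the thing from which participants are withdrawn. Give COVID-19 the same rule there as in the COVID-19 section.
2. State that safety, questionnaire and app follow-up continue after stimulation stops, remotely if needed, unless the participant withdraws consent.
3. State that every randomised participant, including anyone replaced after a positive COVID-19 test, stays in the allocated arm for intention to treat.

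The cost is protocol wording and a little remote contact, with no added visits. With recruitment closed, item 2 can help only those who have not yet reached 4 months. Item 3 can still be set, because the analysis plan is to be signed off before data lock and the article reports that no intervention comparison had been analysed at submission. Replacing listwise deletion with a mixed model is a separate question and is not needed here.

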### Methods in analysis to handle protocol non-adherence and any statistical methods to handle missing data {20c}

Participants’ completion of questionnaires and MRI data with quality check will be confirmed before commencing the intervention, minimising the risk of missing data at the baseline timepoint. For measures that have missing data for a single time-point we will use listwise deletion for all secondary outcomes except for adverse events and treatment compliance (missing data are not possible), assessment of blinding success and MRI. If there is missing data for the blinding assessment, we will also present the number of participants who either declined to guess which intervention they received, or their selection was not recorded. We will use case-wise deletion for missing data at a single MRI time-point (i.e. if only baseline MRI data was collected, the participant will be excluded from all MRI analyses), and listwise deletion for individual MRI metrics, assuming that data are missing at random and unrelated to measurement of myelin content or lesions in the brain.

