## Trial status

Active, Version 5_01 November 2021. First participant recruited Jan 2021. Twenty participants recruited as of October 2021. Expected last participant, last visit by end December 2021. We originally planned to recruit 30 participants; however, due to restrictions related to the COVID-19 pandemic, the study timeframe was truncated. To meet funding-related timelines, recruitment has now been closed at 20 participants. The protocol manuscript was not submitted earlier because recruitment was previously planned to continue to reach 30 participants. At submission, no data have been statistically analysed for intervention comparisons.

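### The withdrawal rule removes participants from the whole study, contradicts the COVID-19 section, and undercuts the promised intention-to-treat analysis of participant-reported outcomes

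*Protocol article*

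**What the plan says.** Section {11b} (Criteria for discontinuing or modifying allocated interventions) states: "Participants will be withdrawn from the study if they develop any contraindications". The list that follows covers pregnancy, a metal implant, seizures, and starting tricyclics, neuroleptics/anti-psychotics or anti-seizure drugs. Its last item covers loss of fitness (for example relapse, a change of disease-modifying therapy, or high-dose steroids) at the clinical PI's discretion, and then continues "test positive for COVID-19; or as an urgent safety measure".

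For a participant who tests positive, the Discussion section on COVID-19 says that "they may be withdrawn from the study intervention and MRI follow-ups; we will complete study questionnaires and assessments remotely".

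Three other sections bear on the consequences:

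- {18b} (retention and follow-up) deals with people who miss more than 3 consecutive visits. They "remain in the study to complete follow-up safety and PROMs" and lose only the follow-up MRI. The same section commits the analysis plan to a per-protocol analysis and an "intention to treat analysis for AE and participant-reported outcomes".
- {20c} (missing data) says: "For measures that have missing data for a single time-point we will use listwise deletion for all secondary outcomes", with exceptions for adverse events, compliance, blinding and MRI.
- Trial status reports that "recruitment has now been closed at 20 participants", against 30 planned.

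**The concern.** Stopping stimulation and leaving the study are different events, and {11b} merges them. For COVID-19 the two instructions conflict in scope (whole study against stimulation and MRI only) and in force (*will* against *may*). For the other triggers no sentence limits the withdrawal to the intervention.

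An intention-to-treat analysis of questionnaires needs questionnaires from people who stopped treatment. If study withdrawal is applied as written, those people give no later data and drop out of the symptom analyses. A seizure, a newly started listed drug, or a relapse (if the PI withdraws the participant) may go with worse symptoms, so the missing scores may differ systematically from the observed ones. None of the triggers prevents a remote questionnaire.

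**Working it through.** The plan states no figure on this point and gives no sample-size calculation to reproduce. The check is a comparison of the text, followed by the cost of one loss.

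**Text comparison**

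| Situation | Section | Stimulation | MRI | Questionnaires |
|---|---|---|---|---|
| Listed contraindication | {11b} | stops | stops (literal reading) | stop (literal reading) |
| Positive COVID-19 test | {11b} | stops | stops (literal reading) | stop (literal reading) |
| Positive COVID-19 test | Discussion, COVID-19 | may stop | may stop | continue remotely |
| More than 3 consecutive missed visits | {18b} | may continue to end of week 5 | no follow-up scan | continue |

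Rows 2 and 3 describe the same event and disagree. Row 4 shows the handling that an intention-to-treat analysis needs, but its trigger is missed visits. The protocol nowhere says outright that follow-up ends after a withdrawal under {11b}. That is the literal reading, and nothing in the text excludes it.

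**From withdrawal to analysis.** A person withdrawn before session 20 lacks both the post-intervention and the 4-month scores. The deletion rule in {20c} is phrased for a single missing time point, but the mixed ANOVAs across three time points need complete records, so this person drops out in any case. The Mann-Whitney tests on change from baseline have no change score for this person either.

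**Cost of one loss**

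Inputs: N = 20 (Trial status); 2:1 allocation, stratified by sex, block size 6 (section {16a}). Assumption: each block holds 4 rTMS and 2 sham.

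- Expected split: 20 × 2/3 = 13.3 and 20 × 1/3 = 6.7, so about 13:7.
- One sham participant is 1/7 = 14.3% of the arm; one rTMS participant is 1/13 = 7.7%.
- Incomplete blocks in two strata allow 4 to 8 sham participants. With strata of 4 and 16, for example, the two complete blocks contribute 4 sham, and the two part-blocks of 4 contribute 0 to 2 each. One sham loss is therefore 1/8 = 12.5% to 1/4 = 25% of the arm.

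The standard error of a between-arm difference, in units of the outcome's SD, is √(1/n₁ + 1/n₂):

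| Split (rTMS:sham) | Before | After one loss | Change |
|---|---|---|---|
| 13:7, sham loss | √(1/13 + 1/7) = 0.469 | √(1/13 + 1/6) = 0.494 | +5.3% |
| 13:7, rTMS loss | 0.469 | √(1/12 + 1/7) = 0.476 | +1.4% |
| 12:8, sham loss | √(1/12 + 1/8) = 0.456 | √(1/12 + 1/7) = 0.476 | +4.2% |
| 16:4, sham loss | √(1/16 + 1/4) = 0.559 | √(1/16 + 1/3) = 0.629 | +12.5% |

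These figures describe lost precision. The documents give no rate for any trigger and no expected scores after one, so the bias cannot be calculated.

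**The case against.** The best defence is that this is loose wording. The heading of {11b} is about interventions, and section {11d} refers back to it as the discontinuation criteria. Both places that say what happens after stimulation is interrupted keep the questionnaires and drop only MRI. {18b} also sets out a retention procedure, with three contacts by two methods. The article condenses a fuller protocol, which may spell out follow-up after each trigger. COVID-19 shares a list item with the PI-discretion clause, so the *will*/*may* conflict could be softer than it looks, and staff would naturally follow the specific COVID-19 section. The arithmetic applies to any dropout and uses a simple two-arm difference, not the planned time-by-group interaction. The symptom outcomes are exploratory in a phase 1 safety trial, and recruitment is over.

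Much of this stands. Continued follow-up was probably intended, the loss of precision is generic and modest, and little conduct remains to be changed. Two points survive. Even if PI discretion covers COVID-19, the scope of withdrawal still differs between the two sections. And the objection is to a rule that the article states, not to a missing detail: a site following the operative sentence would stop collecting data that {18b} needs, and for triggers other than COVID-19 no text corrects it.

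**Conclusion.** The concern holds. The COVID-19 contradiction is explicit. The damage to the intention-to-treat analysis follows if {11b} is applied literally. It affects the secondary symptom outcomes only, because the adverse event that triggers a withdrawal is already counted in the primary outcome. At about 13:7, one sham loss costs 14% of that arm and about 5% in standard error (4% to 12.5% over the possible splits, assuming 4:2 blocks); one rTMS loss costs about 1%. The direction and size of any bias are unknown. This is a change worth making because it is cheap, but it does not threaten the trial's main safety conclusion.

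**What to change.** In {11b}, withdraw participants from the study intervention, and from MRI where it is contraindicated, instead of from the study. Use identical COVID-19 wording in {11b} and the Discussion. State that anyone who stops stimulation remains in follow-up for adverse events, the post-intervention questionnaires and app assessments, and the 4-month remote assessment, unless they withdraw consent to data collection. Leave the clinical criteria for stopping stimulation unchanged.

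Because recruitment is closed, also report by arm how many participants were withdrawn under {11b}, for what reason, and which assessments are missing.

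The cost is a short amendment, one reporting line and a few extra remote contacts through the existing phone and REDCap arrangements. The new wording may reach few participants, so the reporting line may be the more useful part.
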